### Recruitment Procedures

First, members of the PanelCom panel will be invited to participate in the experiment via mass emailing, receiving up to 2 reminders [65]. Second, (former) patients with cancer and their family members will be recruited in collaboration with several cancer patient support organizations, including the Dutch Cancer Society and Hematon, the Dutch association for patients with blood cancer and lymphoma. Through these organizations, potential participants will be informed about the study and invited to sign up for participation.

Participants are informed that the study is part of a research project about information giving in the context of cancer treatment. Furthermore, they are informed that study participation includes an online survey and a scripted video of a hematology consultation that will take approximately 30 min to complete and can be entered from a home computer. Participants are asked to complete the survey individually and in one sitting. Finally, participants will be notified that all data will be treated confidentially and remain anonymous. Participants provide informed consent upon entering the online survey.

### Allocation and Blinding

Participants are automatically and randomly assigned to 1 of 12 conditions, or interventions, (1:1 ratio) in either the structuring or the tailoring experiment. Allocation is achieved by computer-generated randomization. Participants are unaware to which condition, that is, intervention, they are assigned (blinded). Researchers are unaware, for the duration of the trial, to which condition participants are assigned.

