## Methods

### Trial Design

The trial employs a between-subjects single-message factorial design in which the independent variables of interest are systematically manipulated. This is done using the video vignette methodology. In experiment 1, hematologists’ information structuring and expressions of caring are varied in a 2 (standard versus enhanced structuring) × 2 (standard versus enhanced caring) design. In experiment 2, hematologists’ information tailoring and expressions of caring are varied in a 2 (high versus low need for information) × 2 (high versus low amount of information provided) × 2 (standard versus enhanced caring) design. This results in 12 experimental conditions, or interventions, across the trial (see Tables 1 and 2).

**Table 1 table1:** Experiment 1: Manipulation of provider information structuring and caring (2×2 design).

Manipulations	Standard of care	Caring
Standard of care	Standard of care	Enhanced caring
Structuring	Enhanced structuring	Enhanced caring and structuring

**Table 2 table2:** Experiment 2: Manipulation of provider caring and information tailoring in a match/mismatch design (2×2×2 design).

Manipulations		Provider			
		Enhanced caring		No caring	
		Additional information provision	No additional information provision	Additional information provision	No additional information provision

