### Video Vignette Intervention

#### Video Vignettes

Eligible participants are randomized in equal proportions to view 1 of 12 video vignette interventions. Video vignettes are scripted, hypothetical scenarios of real-life (medical) consultations, which allow for the systematic variation of verbal and/or nonverbal behaviors across experimental conditions [48,54-63]. Video vignettes are preferred in health communication research when ethical or practical considerations prevent the manipulation of physician behaviors in clinical practice. Participants are asked to view and evaluate vignettes while imagining themselves to be the patient in the video, that is, participants act as *analogue patients* [61,62]. Several studies demonstrated the validity of this type of methodology [60-63] and show that video vignettes allow for good levels of experimental control through script standardization and manipulation checks. Formal guidelines for video vignette development proposed by Hillen et al [61] and van Vliet et al [62] are used in this study to enhance internal and external validity.

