### Sample Size

The required sample size is estimated at N=420 participants (*structuring* N=180 and *tailoring* N=240), based on *a priori* power analyses in G*Power [75] with the alpha set at .05, a probability level of .80, and estimated medium effect sizes of .10 to .25 for the dependent variables, that is, information recall, information satisfaction, and trust in the physician.

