## Results

Data collection has now been completed. A total of N=607 participants went to our homepage, provided informed consent online, and started the survey. A total of N=470 completed the first part of the survey and were randomized to receive 1 of the 12 video vignette interventions within 1 of the 2 experiments (77.4%, 470/607). Participants did not differ from those who dropped out, except for their age (in experiment 1, N=148): completers were younger (mean 3.8 years; *P*=.002) and consequently less likely to be retired (41.2%, 194/470) vs 56.4% (83/148; *P*=.006)*.* The first analyses will be available in Spring 2019.

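### Equal randomisation over 12 conditions does not give the 180 structuring and 240 tailoring participants that the sample size section requires

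*Protocol article*

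**What the plan says.** All of this is in the protocol article.

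- **Trial Design** gives experiment 1 (structuring) a "2 (standard versus enhanced structuring) × 2 (standard versus enhanced caring) design", which is 4 cells, and experiment 2 (tailoring) a "2 (high versus low need for information) × 2 (high versus low amount of information provided) × 2 (standard versus enhanced caring) design", which is 8 cells. It adds: "This results in 12 experimental conditions, or interventions, across the trial".
- **Sample Size** says: "The required sample size is estimated at N=420 participants (*structuring* N=180 and *tailoring* N=240"). The power analysis behind these sizes is described as run "with the alpha set at .05, a probability level of .80, and estimated medium effect sizes of .10 to .25 for the dependent variables". It names no statistical test and no effect-size metric.
- **Video Vignettes** says: "Eligible participants are randomized in equal proportions to view 1 of 12 video vignette interventions".
- **Allocation and Blinding** gives the rule as follows: "Participants are automatically and randomly assigned to 1 of 12 conditions, or interventions, (1:1 ratio) in either the structuring or the tailoring experiment".
- **Results** reports: "A total of N=470 completed the first part of the survey and were randomized to receive 1 of the 12 video vignette interventions". The article does not clearly say how many of these entered each experiment.

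**The concern.** The two size targets imply different cell sizes in the two experiments, while the two allocation statements imply the same size in every cell. Both cannot describe one randomisation scheme. If the allocation text is right, one experiment recruits fewer people than its own power calculation asked for and the other recruits more.

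The practical risk lies in how the completed trial is read. Someone who sets 470 randomised against 420 required will conclude that both experiments met their targets. Under the allocation as written, structuring would not have. A null result on the overall comparison of the four structuring cells would then be credited with 80% power that it did not have.

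**Working it through.** **Inputs.** From Sample Size: 180, 240, 420, alpha .05, power .80, effect sizes .10 to .25. From Trial Design: 4 and 8 cells. From Video Vignettes and Allocation and Blinding: equal allocation over 12 conditions. From Results: 470 randomised. *Assumption:* the effect size is Cohen's f, the metric G*Power uses for analysis of variance.

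**1. Reproduce the stated sizes.** For a one-way omnibus F test with k cells, df1 = k − 1, df2 = N − k and noncentrality λ = N × f². Power is the probability that a noncentral F(df1, df2, λ) exceeds the central 95% point. Take the smallest N with power of at least .80, rounded up to equal cells, at f = .25:

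- k = 4, df1 = 3: N = 180 (power .804)
- k = 8, df1 = 7: N = 240 (power .807)

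Both match exactly. The alternatives do not: a 1-df main effect at f = .25 needs 128 per experiment; at f = .10 the omnibus test needs 1096 and 1448, and a main effect needs 788 and 792. The omnibus test at f = .25 is therefore a well-supported inference about the planning test, though the article does not state it.

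**2. Cell sizes the targets imply.** 180 / 4 = 45 and 240 / 8 = 30, a 3:2 ratio per cell, or 180:240 = 3:4 between experiments.

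**3. Cell sizes the allocation text implies.**

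- N = 420: 420 / 12 = 35 per cell. Structuring 4 × 35 = 140 (40 short, 40 / 180 = 22%). Tailoring 8 × 35 = 280 (40 over).
- N = 470: structuring 470 × 4 / 12 = 156.7. Tailoring 470 × 8 / 12 = 313.3.

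If randomisation is simple, with probability 1/12 per cell, the chance that structuring reaches 180 of 420 is about 0.00003 (binomial, p = 1/3), so chance imbalance does not close the gap.

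**4. Power at f = .25, equal cells.**

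| Experiment | N | λ = N × .0625 | Omnibus power | 1-df main-effect power |
|---|---|---|---|---|
| Structuring, target | 180 | 11.25 | .804 | .916 |
| Structuring, of 420 | 140 | 8.75 | .684 | .836 |
| Structuring, of 470 | 157 | 9.81 | .740 | .876 |
| Tailoring, target | 240 | 15.00 | .807 | .971 |
| Tailoring, of 420 | 280 | 17.50 | .875 | .986 |
| Tailoring, of 470 | 313 | 19.56 | .915 | .993 |

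**5. If 1:1 refers to the two experiments.** 420 / 2 = 210 each: tailoring is 30 short, with omnibus power .739. 470 / 2 = 235 each: tailoring is 5 short, with omnibus power .796. Structuring then exceeds 180 in both cases.

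**6. Totals that would meet both targets.** Equal cells: 45 × 12 = 540. 1:1 between experiments: 2 × 240 = 480.

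**7. Detectable effect.** With a 1-df test and 80% power, solving for f gives about .225 at 157 and about .16 at 313.

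**The case against.** **The hypothesis itself is not starved of power.** H1 contrasts two levels of structuring, which is a 1-df effect. At f = .25 it needs 128 participants, and it keeps power .84 at 140 and .88 at 157. A reader might infer from .68 or .74 that the test of H1 is underpowered at the planning effect. The documents do not support that: those figures belong to the four-cell omnibus test. This objection stands and limits the consequence. It does not rescue the stated sizes, which only the omnibus test reproduces. Nor is the slack at f = .25 protection over the whole stated range: at f = .10 the 1-df power at 157 is .24, though that problem exists under any split.

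**One reading reconciles the numbers.** If 1:1 means equal allocation within each experiment, with a 3:4 split between experiments, the result is exactly 45 and 30 per cell. A reader might infer that no equal-allocation reading can yield 180 and 240; that is too strong, because this one does. However, no section states a 3:4 split, and Video Vignettes, with equal proportions over all 12, contradicts it. If it is what was done, the allocation text is what needs correcting.

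**The 470 may suffice.** With 1:1 between experiments, 235 in tailoring gives .796, essentially .80. That stands for that reading. With equal cells, structuring remains about 23 short.

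**The article is condensed.** It is, but it states the total, both sub-totals, the cell counts and the ratio. The point is that these stated facts disagree, not that detail is missing.

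A reader might also take the mention of experiment 1 with N = 148 in Results as that experiment's size. The same number is the denominator of the group compared with the 470 completers, so its meaning is unclear and nothing here rests on it.

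**Conclusion.** The inconsistency is real. As written, equal allocation over 12 conditions gives 140 and 280 at N = 420, and about 157 and 313 at N = 470, against stated requirements of 180 and 240. On the omnibus one-way F test at f = .25, structuring power is about .68 or .74 instead of .80. These power figures assume that test and Cohen's f, equal cells, and no loss between randomisation and analysis.

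The documents do not show which statement is wrong. The sample size section may be right and the randomiser weighted, or the allocation sections may be right and the size targets unmet. Nor does the article claim outright that 1:1 allocation produces 180 and 240; the conflict appears only when the sections are put together.

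No bias or type I error inflation follows, and the allocation can no longer be changed. This should be fixed, but it does not threaten the validity of the trial.

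**What to change.** Reconcile Sample Size, Video Vignettes, and Allocation and Blinding:

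1. State the allocation probabilities actually used: equal over the 12 cells, or weighted 3:2 per structuring versus tailoring cell (3:4 between experiments). Say what the 1:1 ratio refers to.
2. Report the numbers randomised and analysed in each experiment.
3. Name the test and effect-size metric behind 180 and 240.
4. Restate the power or detectable effect at the actual numbers. If cells were equal, the 1-df detectable effect at 80% power is f of about .225 at 157 and .16 at 313, and omnibus power for structuring at f = .25 is about .74.

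The cost is about one paragraph of text and no further participants. The downside is a less favourable stated power for structuring if the cells were in fact equal.

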### Analysis

Data will be cleaned in a stepwise procedure [76], including the identification of missing values because of dropout, standardization and normalization of data, and outlier analysis. Data will subsequently be analyzed using IBM SPSS statistical package. In the first step, it will be determined whether the experimental groups, within each of the 2 subexperiments of the trial, are indeed comparable in terms of participant characteristics, such as sociodemographics, personality traits, and disease history. If differences are found, these will be controlled for in subsequent analyses. Then, for each of the 2 experiments, one-way analysis of variance or covariance (when aspects need to be controlled for) will be conducted to test the effects of information structuring, information tailoring, and caring on information recall, satisfaction, and trust (H1, H2, and H3, respectively). Additionally, the interaction effect between caring and information structuring as well as tailoring will be added to these models (RQ1). It will be investigated to what extent patient characteristics moderate the hypothesized relationships (RQ3). If necessary, because of violations of the assumption of homogeneity of variance, Welch F statistic will be employed. Posthoc comparisons, using Bonferroni or Games-Howell, will be used as applicable, to create a better understanding of between-group differences. Finally, linear regression analyses will be used to assess possible relationships of information recall, satisfaction, and trust with expected symptom distress (RQ2). Significance levels are determined at *P*<.05.

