#### Caring

Caring refers to a communication style in which the physician displays behaviors of empathy for and affective engagement with the patient [9,47,48,49], thereby potentially reducing patients’ emotional distress [9,32,48] and enhancing patients’ memory of information [49,50]. A sense of a caring relationship with the physician has been shown to increase patients’ satisfaction with the provided information [34]. Other studies demonstrate that patients’ trust in their physician reduces the need to subsequently seek detailed information [44,51]. Moreover, research suggests that physicians can help alleviate symptom distress by affective communication, rather than by information giving alone [21,52].

The effectiveness of the aforementioned cognitive (ie, structuring and tailoring) and affective (ie, caring) strategies may differ, depending on patients’ individual characteristics known to affect information processing, such as their age [5], their degree of anxiety [35] or coping style [53], or their medical history.

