##### Background Measures

Survey questions concerning participants’ sociodemographic background included gender, birth year, ethnicity, living situation, educational level, and occupational status. In addition, questions concerning participants’ health literacy [68], medical knowledge (general and lymphoma-specific), overall health (1 item), and cancer (treatment and family) history were included. Personality trait measures included the avoidance scale of the Impact of Event Scale (8 items, 4-point scale) [69] to assess the tendency to avoid cancer-related issues, the Trait Anxiety Inventory (20 items, 4-point scale) [70] for the assessment of generalized anxiety, the Threatening Medical Situations Inventory (TMSI-2, Monitoring scale) [71] to assess a monitoring coping style, and a single item assessing information preferences in medical consultations (5-point scale).

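### Covariates for the H1–H3 models are chosen by observed baseline imbalance, not fixed in advance, which costs precision and makes the model depend on the data

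*Protocol article*

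**What the plan says.** In the protocol article, Methods, Analysis, the first step after data cleaning is a comparability check: "it will be determined whether the experimental groups, within each of the 2 subexperiments of the trial, are indeed comparable in terms of participant characteristics". The characteristics named are sociodemographics, personality traits and disease history. The rule that follows is "If differences are found, these will be controlled for in subsequent analyses". The model for H1, H2 and H3 depends on the outcome of that check: "one-way analysis of variance or covariance (when aspects need to be controlled for"). No covariate is fixed for these models.

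No criterion is given for what counts as a difference. The only threshold in the section is its closing sentence, which begins "Significance levels are determined at" and gives P<.05.

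Under Allocation and Blinding: "Allocation is achieved by computer-generated randomization".

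The Introduction (Caring) says that the effectiveness of the strategies "may differ, depending on patients’ individual characteristics known to affect information processing, such as their age [5"], and goes on to name anxiety, coping style and medical history.

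Two other places touch on these variables. RQ3 asks whether patient characteristics moderate the effects. Strengths and Limitations says that the participant's own information preference can be controlled for.

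**The concern.** When groups are formed by randomisation, a baseline difference between them is a chance event. Its presence says nothing about whether the variable predicts recall, satisfaction or trust, and its absence does not make a predictive variable useless as a covariate. Adjustment gains precision because the covariate explains outcome variance, whether or not it is balanced.

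A rule triggered by imbalance therefore selects on the wrong property. It can bring in variables unrelated to the outcome, and it will usually leave out those that matter. It also means that the H1–H3 models cannot be written down before the data are seen. Because the check is run within each experiment, H3, which both experiments test, may be tested with different covariates in each.

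At stake are power on the primary outcomes and the pre-specification of the primary models. This is a rule the article states, not a detail it leaves to an analysis plan.

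**Working it through.** **1. The plan's own figure.** Sample Size gives N=180 (structuring) and N=240 (tailoring) at alpha .05, power .80 and effect sizes of .10 to .25. The metric is not named; I read it as Cohen's f. With the noncentral F for a one-way ANOVA (noncentrality = f²N) and f=.25:
- 4 groups (3 df): N=180, power .804.
- 8 groups (7 df): N=240, power .807.

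Both figures reproduce, at the .25 end of the range only.

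**2. How many characteristics are checked.** Background Measures lists variables that "included gender, birth year, ethnicity, living situation, educational level, and occupational status" (6). It adds health literacy (1), medical knowledge, general and lymphoma-specific (2), overall health (1), cancer history (about 1), three trait scales (3) and information preference (1). The sum is 6+1+2+1+1+3+1 = 15, or 16 if treatment and family history are counted separately. I use 10 to 16.

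**3. Chance of at least one flagged difference per experiment.** Assume a test at .05 for each characteristic, independent tests and correct randomisation:
- 10 characteristics: 1 − .95^10 = .40
- 15 characteristics: 1 − .95^15 = .54
- 16 characteristics: 1 − .95^16 = .56

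Correlation between the characteristics lowers these figures.

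**4. Chance that one given predictor, such as age, is adjusted for.** By construction this is about .05. Simulation gave .046 to .051.

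**5. Power forgone.** The article gives no covariate–outcome correlation, so R² is an assumption. For a 1-df main effect, adjustment turns f into f/√(1−R²). At N=180 (4 cells), alpha .05:

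| f | Unadjusted | R²=.10 | R²=.20 |
|---|---|---|---|
| .10 | .266 | .290 | .320 |
| .15 | .517 | .560 | .609 |
| .20 | .761 | .803 | .847 |
| .25 | .916 | .940 | .962 |

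The table uses one covariate. With six covariates and the same total R², the f=.20 row is unchanged to two decimals. At N=240 (8 cells) and f=.20 the figures are .870, .902 and .932.

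Put another way, the gain is worth a factor 1/(1−R²) in sample size. This is 1.11 to 1.25, or about 20 to 45 participants at N=180 (180×.11 and 180×.25).

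**6. The rule itself, simulated.** 20,000 replicates, N=180, standardised difference 0.4 (f = 0.4/2 = .20), one covariate, adjusted for only if its 4-group baseline test has P<.05:

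| Correlation with outcome | Unadjusted | Rule as stated | Always adjusted |
|---|---|---|---|
| .3 (R²=.09) | .759 | .762 | .795 |
| .5 (R²=.25) | .765 | .773 | .871 |

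The rule performs almost like no adjustment. With no true effect, its type I error across the N=180 and N=240 designs was .044 to .052.

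**The case against.** **The harm is modest.** This stands. Type I error held at about .05. At a correlation of .3 the rule loses about 3 points of power (.762 against .795), and only a strong predictor opens a wide gap. The R² values are assumed.

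**Different covariates make the two H3 estimates non-comparable.** A reader might infer this, but the article does not support it. The models are linear, and in a randomised comparison adjusted and unadjusted mean differences estimate the same quantity. Only their precision differs. Nor does anything in the plan or the simulation point to bias or inflated alpha.

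**Testing at .05 is inferred.** Also true. The Analysis section does not call the check a test, and the P<.05 sentence is not tied to it. The 40–56% and 5% figures depend on that reading and, for the former, on independence. Results itself links age with retirement, so some correlation is certain. Under any other threshold, imbalance would still drive the selection.

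**The check may serve another purpose.** It follows data cleaning, which includes dropout and outliers, and the article does not say whether it covers everyone randomised. If it covers only those analysed, differences could reflect attrition as well as chance. That is a reason to examine differential dropout directly, not to select covariates by imbalance.

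**The article does not ignore these characteristics.** The sentence in the Introduction concerns moderation, and RQ3 takes that up. But RQ3 is a separate question and does not place age, anxiety or coping style in the H1–H3 models. The statement on information preference is optional and covers one variable. That these characteristics predict recall is an inference: the Introduction says they affect information processing, and under Tailoring it links better processing to better recall.

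**Conclusion.** The point holds as a matter of efficiency and pre-specification. The stated rule selects covariates by chance imbalance, separately in each experiment, and leaves out variables the article itself singles out unless they happen to differ.

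For f=.20 at the planned N=180, power is about .76 unadjusted and nearly the same under the rule. With fixed covariates it is about .80 to .85. This rests on an assumed R² of .10 to .20, on reading the effect size as Cohen's f, and on a baseline test at .05. The point should not be carried further to bias, false-positive inflation or a changed estimand.

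The change is worth making because it is cheap, not because the planned analysis would be invalid.

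**What to change.** Replace the imbalance-triggered rule with one short covariate set, fixed before the analyses and used in every H1–H3 model in both experiments regardless of balance. Draw it from the article's own variables: age, trait anxiety, coping style and information preference, optionally with health literacy or educational level.

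First confirm that each was measured before the video. Results implies this by saying that a first part of the survey preceded randomisation, but it does not itemise that part.

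Report baseline characteristics descriptively for all randomised participants, without using them to select covariates. Examine differential dropout between conditions separately. Give the unadjusted model as a sensitivity analysis.

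The change needs no new data if the timing is confirmed. It costs a few degrees of freedom and some rewording. Results describes the first analyses as still to come; any that were run before the set was fixed should be labelled as such.

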### Research Objectives

The randomized controlled trial described in this study protocol aims to provide evidence concerning the pathways linking physician communication to (improved) consultation outcomes for patients. More specifically, it seeks to determine the effects of information *structuring* (experiment 1) and information *tailoring* (experiment 2), combined with physician *caring*, on information recall, satisfaction with information, and trust in the physician (primary objective). Additionally, it aims to determine the effects of these independent variables on expected symptom distress (secondary objective). The planned trial consists of a single study in which 2—analytically distinct—subexperiments can be identified—each with specific objectives related to the independent variables.

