### Hypotheses and Research Questions

The hypotheses and research questions are as follows (see Figure 1):

Experiment 1: StructuringH1: Information *structuring* positively affects patients’ recall of treatment information.Experiment 2: TailoringH2: Information *tailoring* positively affects patients’ recall of treatment information.Experiments 1 and 2: CaringH3: Oncologists’ expressions of *caring* positively affect patients’ recall of, and satisfaction with, treatment information and their trust in the oncologist.RQ1: Is there an interaction effect of information *structuring* or *tailoring* and oncologists’ expressions of *caring*?RQ2: Do patients’ recall of, and satisfaction with, treatment information and their trust in the oncologist affect patients’ expected symptom distress?RQ3: Do patient characteristics, including sociodemographics (eg, gender, age, and health literacy), medical history (eg, type and year of diagnosis and treatment), and personality traits (eg, coping style and trait anxiety), moderate the hypothesized relationships?

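### H3 is one hypothesis for both experiments, but caring is tested only within each, so a balanced randomised caring contrast over all 12 conditions goes unused

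*Protocol article*

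**What the plan says.** Under Hypotheses and Research Questions, H1 belongs to experiment 1 and H2 to experiment 2. H3, on recall, satisfaction and trust, is listed under a joint label: "Experiments 1 and 2: CaringH3".

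Trial Design makes caring a two-level factor in both experiments. Experiment 1 is a "2 (standard versus enhanced structuring) × 2 (standard versus enhanced caring) design". Experiment 2 adds the video patient's information need to a "2 (high versus low amount of information provided) × 2 (standard versus enhanced caring) design".

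Allocation is a single step. Video Vignettes says "Eligible participants are randomized in equal proportions to view 1 of 12 video vignette interventions", and Allocation and Blinding says participants are "automatically and randomly assigned to 1 of 12 conditions, or interventions, (1:1 ratio) in either the structuring or the tailoring experiment".

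Analysis then says that "for each of the 2 experiments, one-way analysis of variance or covariance (when aspects need to be controlled for) will be conducted", at P<.05. It describes no analysis of caring across experiments. Research Objectives presents one study in which "2—analytically distinct—subexperiments can be identified".

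**The concern.** Structuring and tailoring each exist in one experiment only, so H1 and H2 have to be tested there. Caring is different. It is the same manipulation, added to the same basic script, and crossed with the other factors in all 12 conditions. Six conditions have enhanced caring and six do not, so the contrast over the whole trial is itself randomised and balanced. The plan does not use it.

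Two things follow. Each test of H3 works with part of the available information. And one hypothesis receives two verdicts per outcome, with no stated way to read a result that is significant in one experiment only. Counting either result as support, or requiring both, gives very different error rates, and that choice could be made after the results are seen.

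**Working it through.** **Inputs.** Sample Size gives 180 (structuring) + 240 (tailoring) = 420, "with the alpha set at .05, a probability level of .80, and estimated medium effect sizes of .10 to .25 for the dependent variables". The metric is not named; it is read here as Cohen's f, which for a balanced two-level factor is half the standardised mean difference. Equal allocation over 12 conditions would instead split 420 as 4 × 35 = 140 and 8 × 35 = 280, so both splits are shown. Results reports 470 randomised, about 157/313 if the conditions are equal.

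**Formula.** Power = P(F′ > F.95(df1, N − g)), where F′ is noncentral F with λ = N·f² and g is the number of conditions in the model.

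**The plan's own figures.** With the one-way omnibus test at f=.25 and 80% power, 4 groups (df1=3) need 179, or 180 in equal groups. Eight groups (df1=7) need 237, or 240. Both planned numbers are reproduced, which supports reading the metric as f. At f=.10 the same test needs 1,096 and 1,448, so the plan was sized at the top of its stated range.

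**Share left out of each caring test.** Experiment 1 omits 240/420 = 57% (planned split) or 280/420 = 67% (equal conditions). Experiment 2 omits 180/420 = 43% or 140/420 = 33%.

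**Power of the caring contrast (df1=1), split 180/240.** For example, at f=.15, λ = 180 × .0225 = 4.05, 240 × .0225 = 5.40 and 420 × .0225 = 9.45. With separate powers a and b, the chance that exactly one test is significant is a(1−b) + b(1−a).

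| f | Exp 1 | Exp 2 | Pooled | Exactly one significant |
|---|---|---|---|---|
| .10 | .266 | .339 | .534 | .425 |
| .15 | .517 | .638 | .866 | .495 |
| .20 | .761 | .870 | .983 | .307 |
| .25 | .916 | .971 | .999 | .108 |

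The smallest f with 80% power is .210, .182 and .137 respectively.

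**Other splits at f=.15.** With 140/280: .42/.71/.87, exactly one significant in 53%. With 157/313: .46/.75/.90, exactly one significant in 52%.

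**The unstated decision rule.** If either test counts as support, type I error per outcome is 1 − .95² = 9.75%. If both are required, power at f=.15 is .517 × .638 = .33. The pooled test has 5% and .87.

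**How well the interaction checks a common effect.** Suppose caring has f=.15 in one experiment and none in the other. The difference is 2 × .15 = .30 SD, with standard error √(4/180 + 4/240) = .197, so z = 1.52 and power is about 33%. With 140/280 it is about 31%.

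**The case against.** The best defence is that the separation is declared. Research Objectives calls the subexperiments analytically distinct, and Analysis follows that. Listing H3 under both experiments can mean that it is to be tested in each, as a built-in replication. Each test holds its 5% level. This stands: separate testing is a legitimate choice and biases nothing. What remains is that no reason is given for splitting the one hypothesis the experiments share.

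Second, a common caring effect is an assumption. RQ1 asks whether caring interacts with structuring or tailoring, and the experiment 2 vignettes add information-need prompts and varying amounts of information. This also stands. The pooled test estimates an average over two vignette sets, and with about 31-33% power in the case above, a non-significant interaction would not show that the effects are alike.

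Third, f=.15 is close to where disagreement is most likely. At f=.25 pooling adds only 8 and 3 points, and disagreement falls to 11%. That is correct, and it is why the whole range is shown.

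Fourth, combining results may be left to a fuller analysis plan. The absence of a combining rule is therefore not counted as an error by itself. The point rests on what the article does fix: the unit in which H3 is tested.

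**Conclusion.** The point holds as a loss of efficiency, not as an error. Pooling raises power for H3 substantially for f between .10 and about .20 (at .15, from .52 and .64 to .87). It changes little at .25, and it does not rescue f=.10, where pooled power is .53 and 80% would need about 787 participants.

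Three stronger readings are not supported:

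- **The separate tests are invalid or biased.** They are neither.
- **Each test ignores at least half of the information on caring.** This is true of experiment 1 only.
- **One significant and one non-significant result contradict each other.** They need not. With a common true effect this pattern is often chance, and a single overall test would prevent it from being misread.

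The figures assume Cohen's f, balanced caring groups within each experiment, the same caring effect and variance in both, and no loss after randomisation. They also credit the separate analyses with a 1-df caring contrast. If the one-way omnibus test were used and only caring had an effect, separate power would be lower: .17/.16 at f=.10 and .80/.81 at f=.25.

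**What to change.** Before the outcome analysis, name the caring main effect in one model over all 12 conditions as the overall H3 test for each of recall, satisfaction and trust. Include terms for experiment and for the condition structure (structuring, information need, information amount). Beside it, report the caring estimate with its confidence interval in each experiment, and the caring-by-experiment interaction. State that the overall test estimates an average effect and that the interaction has low power, so that readers judge consistency from the two estimates. H1, H2 and RQ1 stay within their own experiment.

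The cost is one further model per outcome on data already collected, with no new participants. Because data collection is complete, the change should be dated and recorded as made before the outcome data were analysed. If that is no longer possible, the pooled result should be labelled supplementary.
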